**Methods:**

We will recruit 60 healthy subjects. The participants will be randomly divided into a treatment group, a control group, a sham electroacupuncture group and a blank group, at a 1:1:1:1 ratio. The primary outcome will be determined by the change from baseline to 36 h in the MoCA score. The secondary results include the amplitude and latency of ERP N2 and P3, Go-hit rates, Go-RTs, No-Go-FA rates, the WCST, the Digit Span Subtest of the WAIS, the ESS score and FS-14. The 15 healthy subjects will not receive acupuncture treatment and ASD, but will receive EEG records and cognition functions test at the beginning and end of the experiment. Electroacupuncture intervention will be performed for 30 min once every 12 h, a total of three times. ERP measurements and other tests will be performed after baseline and ASD, and the statistician and outcome evaluator will be blinded to treatment allocation.

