### Sample Size

According to the pre-test study, the average MoCA scores in the treatment group, control group, and blank group are 26.70, 25.72, and 27.32, respectively, and the standard deviations are 1.03, 1.59, and 1.37, respectively. Using the sample size calculation method of multi-group mean, the sample size estimation [one-way analysis of variance (ANOVA)] *F*-test] method will use the test level α = 0.05 (bilateral) and test efficiency 1 – β = 0.90. The bilateral test will be used. The total sample size of 45 cases was estimated using PASS 15.0 software.

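### The sample-size inputs give about 81% power at 45 subjects, not the stated 90%, and the calculation omits the sham arm

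*Protocol article*

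**What the plan says.** The Sample Size section of the protocol article bases its calculation on pilot values: "the average MoCA scores in the treatment group, control group, and blank group are 26.70, 25.72, and 27.32, respectively". In the same order it gives SDs of 1.03, 1.59 and 1.37. The method is the F-test of a one-way ANOVA, two-sided alpha is 0.05, and the target is "test efficiency 1 – β = 0.90". The result reads: "The total sample size of 45 cases was estimated using PASS 15.0 software". That is 15 in each of the three groups with inputs.

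The abstract describes a larger design. It says "We will recruit 60 healthy subjects" and allocates them to "a treatment group, a control group, a sham electroacupuncture group and a blank group, at a 1:1:1:1 ratio", so 15 per arm in four arms. Study Setting repeats the total of 60 and gives the sham group the task of excluding placebo effects. The article gives no MoCA mean or SD for sham and no step from 45 to 60.

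The abstract defines the primary outcome as the change in MoCA from baseline to 36 h. The pre-test values, at 26 to 27 on a 30-point scale, are scores, not changes.

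**The concern.** Every input that the F-test needs is printed, so the total can be checked directly, and it does not reproduce. This is the only power statement in the article, and it concerns the primary outcome. A reader of a null result would take the type II error of the described test to be 10%, when the stated inputs imply about 19%.

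The calculation also describes a three-group design. Enrolling 60 does not repair it, because the three groups in the calculation still have 15 subjects each. The fourth arm, which carries the placebo comparison, has no stated assumption behind its size.

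**Working it through.** **Inputs (Sample Size section).** Means 26.70 (treatment), 25.72 (control), 27.32 (blank); SDs 1.03, 1.59, 1.37; alpha 0.05; three equal groups; total 45, so n = 15.

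**Effect size.**
- Grand mean = (26.70 + 25.72 + 27.32)/3 = 26.58.
- Deviations 0.12, −0.86, 0.74; squares 0.0144, 0.7396, 0.5476; sum 1.3016.
- SD of the means = √(1.3016/3) = 0.659.
- Common SD (root-mean-square) = √((1.0609 + 2.5281 + 1.8769)/3) = √1.8220 = 1.350.
- f = 0.659/1.350 = 0.488.

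**Attempt to reproduce 45 at 90%.** λ = n × 1.3016/1.8220, with degrees of freedom 2 and 3n − 3, and power from the noncentral F distribution.

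| n per group | Total | Power |
|---|---|---|
| 14 | 42 | 0.783 |
| 15 | 45 | 0.814 (λ = 10.72) |
| 18 | 54 | 0.886 |
| 19 | 57 | 0.904 |

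Fifteen per group is the smallest size that reaches 80%; 90% needs 19 per group.

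**Sensitivity to the common SD.**

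| Common SD | Power at n = 15 | Total for 90% |
|---|---|---|
| Root-mean-square, 1.350 | 0.814 | 57 |
| Arithmetic mean, 1.330 | 0.826 | 57 |
| Geometric mean, 1.309 | 0.839 | 54 |
| Median, 1.37 | 0.802 | 60 |
| Largest, 1.59 | 0.668 | 78 |
| Smallest, 1.03 | 0.968 | 36 |

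No row gives 45. Simulation with the three unequal SDs gives about 0.78 for the classical F-test at n = 15. Power of 0.90 at n = 15 needs a common SD of about 1.20, which no ordinary pooling yields. A large-sample chi-square approximation gives 0.843 at n = 15 and needs 18 per group (54). Alpha 0.10 gives 0.891 and needs 48, and it contradicts the stated 0.05.

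**Four arms, 15 each.** The sham mean is an assumption; common SD 1.35.

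| Assumed sham mean | Power |
|---|---|
| 25.72 (equal to control) | 0.902 |
| 26.21 (midway) | 0.795 |
| 26.70 (equal to electroacupuncture) | 0.765 |

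**The treatment contrast.** The treatment group contributes only 0.0144 of the 1.3016 sum of squares, so the F-test is driven by control versus blank (27.32 − 25.72 = 1.60). For electroacupuncture versus control the difference is 26.70 − 25.72 = 0.98 and the SD is √((1.03² + 1.59²)/2) = 1.34. A two-sided t-test with 15 per arm then has power 0.49, and the difference detectable at 80% power is about 1.42 points.

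**Scores versus change.** With equal SDs at both times and baseline-to-36 h correlation ρ, the SD of change is SD × √(2(1 − ρ)). This equals the score SD only at ρ = 0.5. The article gives no ρ. If the score differences are taken as differences in change:

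| Assumed ρ | Electroacupuncture versus control | Three-group F-test |
|---|---|---|
| 0.3 | 0.37 | 0.66 |
| 0.5 | 0.49 | 0.81 |
| 0.7 | 0.70 | 0.96 |

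**The case against.** The strongest reply is that the trial as run has four arms and 60 subjects, and that its F-test may well reach 90%. That is possible: power is 0.902 if sham equals control, and higher if the sham mean lies lower still. A reader might infer that the trial's type II error is at least 19%. The documents do not support that, because the four-arm figure depends on a sham mean they do not give. The reply does not rescue the printed statement, however, which reports a three-group total of 45 and assumes nothing about sham.

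A second reply is that the primary outcome is a change score, so the score-based figures may not describe it. This stands. The 81%, the 49% and the 1.4 points all apply to MoCA scores, and a high correlation would raise power. It does not explain the stated 90%, since the calculation uses score means and SDs and cites no correlation.

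Third, the Discussion already lists the small sample as a limitation. That is fair, but it neither corrects the 90% nor connects 45 to 60.

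**Conclusion.** The power statement is wrong as written. On the article's own inputs, 45 subjects in three groups give about 81% power, so the type II error of that test is about 19%, nearly double the stated 10%. This rests on the root-mean-square SD, the standard choice for this test; other reasonable choices give 80 to 84%, and none gives 45 at 90%.

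The omission of the sham arm is also established. Its consequence is that four-arm power is unknown, not that it is low: the range of about 0.76 to 0.90 rests wholly on assumed sham means between electroacupuncture and control.

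A reader might also conclude that the primary comparison has 49% power, or that the trial must enrol more subjects. Neither follows. The 49% carries over to change from baseline only if the correlation is about 0.5, and no passage settles what power the investigators should accept.

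**What to change.** Restate the Sample Size paragraph to say that:

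- 15 per arm gives about 81% power (type II error about 19%) for the three-group F-test on the pre-test MoCA scores, and 90% would need 19 per group (57);
- the sham arm of 15 was added without a power calculation;
- electroacupuncture versus control (0.98 points, SD 1.34) has about 49% power at 15 per arm, with about 1.4 points detectable at 80%;
- these figures apply to MoCA scores, and carry over to change from baseline only under an assumed baseline-to-36 h correlation of about 0.5.

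If the pre-test data allow it, the correlation should be reported and the figures redone for change. The cost is one rewritten paragraph and a less favourable stated power. Keeping 15 per arm or enlarging the groups remains the investigators' decision.

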## Recruitment

All participants will be recruited through advertisements on websites and posters at colleges and universities near Henan University of Traditional Chinese Medicine. Treatment and measurements will be performed in quiet rooms. Participants will contact the recruitment staff by telephone or WeChat. Recruitment staff will be responsible for the enrollment of participants. If they meet the study criteria, they will be invited to the study. Eligible candidates will be asked to sign an informed consent form before the experiment begins. We will provide accommodation and meals during the experiment, and provide the participants a certain reward at the end of the experiment.

## Inclusion Criteria

Recruitment conditions are as follows: (1) male college student in good health after physical examination; (2) 18–24 years of age and right-hand according to the modified Edinburgh Handedness Questionnaire; (3) normal or corrected-to-normal visual acuity; (4) normal state of sleep awakening, with no unusual sleep schedule–that is, waking up unusually early or late–and no history of shift; the self-made “sleep log” table and interview show that the subjects have good sleep habits; (5) on Symptom Checklist 90 (Symptom List-90 SCL Mel 90), the total average score is <1, and the score of each factor is <1; (6) the score of the Pittsburgh Sleep Quality Index (PSQI) is <5; (7) no habit of drinking coffee, tea, or alcohol or smoking; (8) voluntarily signing an informed consent form. The participants will be contacted a few days later to determine whether they are interested in participating, and, if so, an appointment will be made for them to physical examination package at the Third Affiliated Hospital of Henan University of Traditional Chinese Medicine.

## Exclusion Criteria

Participants with any of the following conditions will be excluded: (1) having taken sedative or sleep-aiding drugs, such as estazolam or alprazolam, in the past month; (2) having received acupuncture or moxibustion treatment in the past month; (3) severe heart, liver, or kidney disease, mental illness, or coagulation dysfunction; (4) family history of mental illness or history of infectious diseases; (5) allergies, especially to needles; (6) implantation of a cardiac pacemaker or implantable electronic equipment.

## Dropout Criteria

(1) Those who do not fill in the cases in a timely and accurate manner or those who do not fill in the cases properly; (2) those who fail to follow the plan for treatment in the course of the trial; (3) subjects who automatically asked to withdraw.

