## Outcomes

### Primary Outcome

The primary outcome is the MoCA score. The cognitive areas assessed include attention and concentration, executive function, memory, language, visual structure skills, abstract thinking, calculation and orientation, with a total score of 30. The lower the score, the more severe the cognitive impairment.

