### Ethics and Dissemination

All candidates who agree to participate and who meet all of the inclusion criteria and none of the exclusion criteria will be provided an informed consent form to provide them with full understanding of what the study participation will entail and the potential risks. Participants have the right to discontinue participation at any time. Data will be used in the aggregate only, and no identifying characteristics of individuals will be published or presented. In the consent form, the participants will be asked if they agree to the use of their data, should they choose to withdraw from the trial. The participants will also be asked for permission for the research team to share relevant data with people from the regulatory authorities, where relevant. This trial does not involve collecting biological specimens for storage. The study conforms to the principles of the Declaration of Helsinki. Ethical approval has been obtained from the IEC of the Third Affiliated Hospital of Henan University of Chinese Medicine. The trial protocol has been registered at the Chinese Clinical Trial Registry. The results will be disseminated through journal articles, a master's thesis, or conference presentations.

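### Two of the three dropout criteria can be read as taking randomised subjects out of the trial for non-adherence or poor form completion, which could bias the comparison in either direction

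*Protocol article*

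**What the plan says.** The Dropout Criteria section lists three grounds:

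1. Form completion: "Those who do not fill in the cases in a timely and accurate manner or those who do not fill in the cases properly".
2. Adherence: "those who fail to follow the plan for treatment in the course of the trial".
3. The subject's own decision: "subjects who automatically asked to withdraw".

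The section gives no consequence for any of them. It does not say whether such a subject stops the intervention, misses the 36-h assessment or leaves the analysis.

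Three other places bear on the point:

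- **Outcome and timing.** The abstract states: "The primary outcome will be determined by the change from baseline to 36 h in the MoCA score". Table 1 schedules MoCA at baseline and at 36 h only, and places allocation before both.
- **Data after withdrawal.** Under Ethics and Dissemination, "the participants will be asked if they agree to the use of their data, should they choose to withdraw from the trial". This covers the third ground only.
- **Analysis.** The Data Analysis section plans repeated measures ANOVA for the behavioural and ERP data. It does not mention subjects who meet a dropout criterion.

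**The concern.** Criteria (1) and (2) describe things that happen after randomisation. Poor form completion and departures from the plan are usually recorded as deviations, and the subject stays in the trial. Here they sit in the same list as withdrawal.

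The Background section itself says that sleep deprivation affects attention, memory and alertness. A subject hit hard by 36 h awake may therefore be more likely to doze, miss a session or complete a form badly. On MoCA, "The lower the score, the more severe the cognitive impairment", so losing such subjects would raise the mean of the arm that loses them.

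Criterion (2) also has different scope in each arm, because the plan to be followed differs. If subjects lost this way are neither measured at 36 h nor analysed, the groups compared are no longer the groups that were randomised. The bias could favour or disfavour electroacupuncture, depending on which arm loses its poorer performers.

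**Working it through.** **Step 1. What following the rule would do.** The article gives no dropout rate, so there is no figure of its own to reproduce on this point. MoCA has one post-baseline measurement. A subject who leaves before 36 h therefore has no change score, and a standard repeated measures ANOVA uses complete cases.

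**Step 2. Scope of criterion (2) by arm.**

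| Arm | Plan to be followed (Intervention sections) |
|---|---|
| Treatment | Needling sessions and 36-h sleep deprivation |
| Sham | Sham needling sessions; other settings as in the treatment group |
| Control | 36-h sleep deprivation only |
| Blank | Neither |

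Criterion (1) can apply in all four arms. Criterion (2) has most scope in the needled arms and hardly any in the blank arm.

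**Step 3. Inputs for a worst-case illustration.**

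- Arm size: the abstract has 60 subjects "randomly divided into a treatment group, a control group, a sham electroacupuncture group and a blank group, at a 1:1:1:1 ratio", so 60/4 = 15 per arm nominally.
- Pre-test MoCA (Sample Size section): treatment mean 26.70, SD 1.03; control mean 25.72, SD 1.59. Difference: 26.70 − 25.72 = 0.98 points.
- Assumption: the lowest one, two or three of 15 scorers are lost, from one arm only, with normally distributed scores.

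**Step 4. Shift in the arm mean.** If the k lowest of n are removed, the mean of the rest rises by

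shift = SD × (sum of the k lowest expected normal order statistics, sign reversed) / (n − k).

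For n = 15 the two lowest expected values are −1.736 and −1.248.

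- k = 1: 1.736/14 = 0.124 SD.
- k = 2: (1.736 + 1.248)/13 = 2.984/13 = 0.230 SD.

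A simulation of 200,000 arms of 15 agrees and adds k = 3:

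| Lowest scorers lost | Shift at SD 1.03 | % of 0.98 | Shift at SD 1.59 | % of 0.98 |
|---|---|---|---|---|
| 1 | 0.128 | 13% | 0.198 | 20% |
| 2 | 0.237 | 24% | 0.366 | 37% |
| 3 | 0.338 | 34% | 0.521 | 53% |

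**Step 5. Effect on the error rate.** With no true effect, equal SDs and the same loss from one arm only, the two-sided 5% error of a two-arm t-test rises to about 7%, 11% and 16% for one, two and three lost (20,000 simulated trials).

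**Step 6. Less selective loss.** If the tendency to be lost correlates 0.5 with the score (assumption), the expected shift halves. For two lost it is 0.5 × 0.237 = 0.12 points at SD 1.03, or 0.5 × 0.366 = 0.18 at SD 1.59. Loss unrelated to the score gives no expected shift, and equal selective loss in two arms with equal SDs cancels.

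**The case against.** The strongest reply is that the section classifies dropouts and stops there. It does not say that they leave the analysis, skip the 36-h assessment or are replaced. Analysis populations and missing-data handling are commonly left to an analysis plan, and that plan is not shown. The consent question on withdrawn subjects' data also shows that ending participation and leaving the dataset are not treated as the same thing.

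The setting also makes such losses less likely. Subjects are screened healthy students. The Go/No-Go section has ten staff accompanying them through the deprivation, and Data Management and Monitoring promises close supervision of outcome assessment and form completion. The article reports nothing that links form quality or adherence to MoCA.

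Much of this stands. A reader might infer that the protocol excludes these subjects from the analysis, or that the losses will be informative and unequal between arms. The documents support neither as fact: the first is a natural reading of the heading, and the second is a plausible mechanism. Nor should 37% be taken as the expected size for two losses. It uses the control SD, the largest available; the treatment SD gives 24%.

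The reply does not dispose of the point. Criteria (1) and (2) are stated rules, so this is more than a detail deferred to an analysis plan. The consent question reaches only those who choose to withdraw. An analysis plan that keeps everyone cannot recover a 36-h MoCA that was never taken because the subject had already been treated as a dropout.

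**Conclusion.** The point holds in a limited form, and the wording should be changed. On its natural reading, the section lets randomised subjects be lost for post-allocation reasons that may relate to the outcome and that cannot apply equally across arms. Nothing shown keeps them in. The direction of any bias cannot be determined from the documents.

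The worst-case range is 0.13 to 0.34 MoCA points at SD 1.03 and 0.20 to 0.52 at SD 1.59, or 13% to 53% of the pre-test difference. It rests on loss from one arm only, of exactly the lowest scorers, with 15 per arm. It also applies the SDs of MoCA scores, because the article gives no SD for the change from baseline, which is the primary outcome. The true effect may be far smaller, and would be nil if every randomised subject is in fact measured and analysed.

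**What to change.** - Reword criteria (1) and (2) as protocol deviations to be recorded, and keep dropout for subjects who withdraw.
- State that the 36-h MoCA, Go/No-Go task and EEG are obtained on every randomised subject who has not withdrawn consent, whatever their adherence or form completion.
- Make the primary analysis all randomised subjects in their allocated group, with the adherent subset as a sensitivity analysis.
- Use the data of subjects who withdraw where they agreed to this on the consent form.

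This concerns assessment and analysis only; it leaves untouched any decision on whether a subject continues the intervention. The cost is protocol and analysis-plan wording, plus the 36-h assessment of a few subjects who might otherwise have left. The downside is slight dilution of the estimated effect by non-adherence, which the sensitivity analysis helps to show.

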## Randomization

Unrestricted (simple) randomization will be used to allocate participants to either the treatment group, control group, blank group. Participants will be randomized using sequentially numbered, opaque sealed envelopes (SNOSE) to maintain allocation concealment (38). Different personnel will carry out tasks such as assigning a sequence, recruiting subjects, or intervention.

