## Methods/Design

### Study Setting

This study is a participant-, statistician-, and assessor-blinded parallel randomized control clinical trial. The study will follow the principles of the Consolidated Standards of Reporting Trials (CONSORT) as well as the Standards for Reporting Interventions in Clinical Trials of Acupuncture (STRICTA) statement for acupuncture. Sixty healthy college students will be randomly assigned to a treatment group, a sham electroacupuncture group and a blank group, at a 1:1:1:1 ratio. The control group will be set to evaluate the efficacy of electroacupuncture. The sham electroacupuncture group be set to rule out placebo effects. The study will be conducted at the Third Affiliated Hospital of Henan University of Traditional Chinese Medicine, Department of Acupuncture, Henan, China, following the Standard Protocol Items: Recommendations for Interventional Trials (SPIRIT). For the participant timeline, see Table 1.

**Table 1 T1:** SPIRIT figure for schedule of enrollment, interventions and assessments.

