## Placebo Group

Placebo group is intervened with sham electroacupuncture. The sham GV20 point is 0.5 cun (≈12.5 mm) lateral to GV20, the sham EX-HN1 point is 0.5 cun (≈12.5 mm) horizontal to EX-HN1 and the sham GV24 point is 0.5 cun (≈12.5 mm) horizontal to GV24, pierce of 3–5 mm following an angle of 0–15°. Procedures, electrode placements, and other treatment settings are the same as in the treatment group but with no electricity output and needle manipulation for de qi.

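### Simple randomisation of 60 people to four arms leaves the implied 15 per arm to chance, and the Randomization section does not name the sham arm

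*Protocol article*

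**What the plan says.** The Methods paragraph of the Abstract is the one place where an allocation statement names every arm. It says "We will recruit 60 healthy subjects" and divides them into "a treatment group, a control group, a sham electroacupuncture group and a blank group, at a 1:1:1:1 ratio". It also gives a count for the blank arm: "The 15 healthy subjects will not receive acupuncture treatment and ASD".

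Study Setting says the participants will be "randomly assigned to a treatment group, a sham electroacupuncture group and a blank group, at a 1:1:1:1 ratio". That is three names with a four-part ratio. The following sentence does mention a control group and its purpose.

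The Randomization section gives the method and a different list of three: "Unrestricted (simple) randomization will be used to allocate participants to either the treatment group, control group, blank group". Concealment follows: "Participants will be randomized using sequentially numbered, opaque sealed envelopes (SNOSE) to maintain allocation concealment". The section also separates the staff who assign the sequence, recruit and intervene. The article mentions no blocking, stratification, minimisation or cap on arm size.

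The sham arm has its own section: "Placebo group is intervened with sham electroacupuncture".

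The Sample Size section derives a total of 45 from a one-way ANOVA on three groups (treatment, control, blank).

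**The concern.** Two things in the allocation text need attention.

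**The list of arms.** The two Methods sections that define allocation each name three of the four arms, and not the same three. The Randomization section is the text from which a list would be drawn up, and it omits sham, the arm that Study Setting says is there to rule out placebo effects.

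**The method.** Unrestricted randomisation leaves the arm sizes to chance. The design implies 15 per arm: the Abstract states this for the blank arm, and it follows for the others from 60/4 and from 45/3. At this size chance imbalance is large relative to 15. A poor draw costs precision in the comparisons of electroacupuncture with sham or with no treatment, and the protocol's Discussion already lists small sample size as a limitation.

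**Working it through.** **Inputs.** 60 participants and four arms at 1:1:1:1 (Abstract). Pre-test MoCA means 26.70, 25.72 and 27.32, SDs 1.03, 1.59 and 1.37, two-sided α 0.05, power 0.90 and total 45 (Sample Size). No MoCA value is given for sham.

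**1. The plan's own figure.**
- Grand mean = (26.70 + 25.72 + 27.32)/3 = 26.58.
- Squared deviations: 0.12² + 0.86² + 0.74² = 0.0144 + 0.7396 + 0.5476 = 1.3016.
- Mean variance = (1.0609 + 2.5281 + 1.8769)/3 = 1.822, so the root-mean-square SD is 1.35.
- With n per arm, the noncentrality is λ = n × 1.3016/1.822. At n = 15, λ = 10.72, and the noncentral F with 2 and 42 degrees of freedom gives power 0.814.
- Power 0.90 is first reached at n = 19 per arm, a total of 57. The stated 45 is therefore not reproduced at 0.90 with this SD. That is a separate matter. Here 0.814 serves only as the equal-arms reference.

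**2. Chance of exactly 15 per arm.** The arm sizes are multinomial(60; ¼, ¼, ¼, ¼):

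P(15, 15, 15, 15) = 60!/[(15!)⁴ × 4⁶⁰] = 0.0021, about 1 in 467.

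**3. Spread of arm sizes.** One arm is binomial(60, 0.25): mean 15, SD = √(60 × 0.25 × 0.75) = 3.35, 2.5th to 97.5th percentiles 9 to 22. From 1,000,000 simulated allocations:

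| Quantity | Value |
|---|---|
| Mean smallest arm | 11.1 |
| Mean largest arm | 19.1 |
| P(some arm ≤ 11) | 0.54 |
| P(some arm ≤ 10) | 0.33 |
| P(largest − smallest ≥ 5) | 0.84 |
| P(largest − smallest ≥ 10) | 0.30 |

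**4. Precision of a two-arm comparison.** The variance relative to 15 per arm is (1/n₁ + 1/n₂)/(2/15). For example, 11 and 11 give (2/11)/(2/15) = 1.364. Over simulated allocations the mean is 1.057. The 95th percentile is 1.35 to 1.36 depending on the simulation run, because the ratio takes discrete values there.

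**5. Power of the three-group ANOVA.** This takes the simulated sizes of three of the four arms, the pre-test means and SD 1.35. Average power is 0.798 against 0.814 with equal arms, a loss of about 1.7 points. The 95% range over allocations is 0.66 to 0.89, so an unlucky draw loses about 15 points (0.814 − 0.66).

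**6. Permuted blocks.** Fixed blocks of 4 give 60/4 = 15 complete blocks and exactly 15 per arm. If blocks of 4 and 8 are equally likely (an assumption) and the list is simply cut at 60, it ends mid-block with probability about 1/3. The four places used from that block of 8 contain one of each arm with probability 2⁴/C(8,4) = 16/70 = 0.229. So 1/3 × (1 − 0.229) ≈ 26% of lists miss 15 per arm, by at most one in any arm. Requiring the list to end on a complete block at 60 removes this.

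**The case against.** The arithmetic is not in dispute. The case for leaving the method alone is about what the arithmetic means, and much of it stands.

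- **Ratio.** A reader might infer that simple randomisation contradicts 1:1:1:1. It does not. The ratio can mean equal allocation probabilities, which simple randomisation satisfies. Only the blank arm is given a count, and that can be read as a planned number; 15 elsewhere is inferred.
- **Validity.** Simple randomisation introduces no bias and does not disturb the type I error. Exact equality is not needed for a valid analysis, so the 0.2% shows only that the implied sizes will not occur. The average loss of power is under two points.
- **Which arm is small.** The 54% and 33% refer to any of the four arms, blank included, not to one particular treatment comparison.
- **Forced counts.** A reader might infer that staff would close an arm at 15 and so make later assignments predictable. Nothing in the article describes this, and the sealed envelopes and separated staff roles are stated safeguards.
- **Missing sham arm.** A reader might infer that sham could be left out of the trial. The Abstract, Study Setting, Placebo Group section and Discussion all include it, so this is a drafting slip. The omission of control in Study Setting is narrower still, since the next sentence names it.
- **Unpredictability.** The arms are visibly different and the acupuncturist is not blinded, so a preference for unpredictable assignments is defensible.

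Two things are left standing: the allocation text needs correcting whatever method is used, and the risk of a poor draw can be avoided at almost no cost.

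**Conclusion.** The point holds as a cheap improvement of moderate severity. The Randomization section omits sham, and the allocation sentence in Study Setting omits control; both need correcting. Simple randomisation is valid here but inefficient. Its effect is small on average (step 5), and the reason to change is the unlucky tail: about a third more variance in a two-arm comparison, or ANOVA power down to about 0.66. The documents do not support calling it a source of bias, a contradiction of the ratio or an error that invalidates the trial.

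The figures assume equal allocation probabilities, all 60 randomised and none lost. The power figures also rest on the pre-test means and a common SD of 1.35. They cover only treatment, control and blank, because the article gives no sham value.

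**What to change.** Replace simple randomisation with a computer-generated permuted-block list at 1:1:1:1 across treatment, sham electroacupuncture, control and blank. Vary the block sizes at random (for example 4 and 8), keep them from recruiting staff, and constrain the list to end on a complete block at 60, which gives exactly 15 per arm. Keep the sequentially numbered opaque envelopes and the separation of staff roles. Name the four arms identically in Study Setting and Randomization.

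The cost is a new list, refilled envelopes and two corrected sentences, all before the first participant is allocated. The downside is that some block ends may be guessable because staff can see which arm a participant is in. Varying and concealing the block sizes limits this but does not remove it.
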